**Figure 1 F1:**
[figure not shown]
Study timeline of the PROMISS trial. aBW, adjusted body weight; BMI, body mass index; MMSE, Mini-Mental State Examination; PROMISS, PRevention Of Malnutrition In Senior Subjects in the EU.

**Table 1 T1:** Measurements and time of measurements in the PROMISS trial

		Timeline				
		Screening (phone)	Screening visit (prior baseline)	Baseline visit	3-month FU visit	6-month FU visit
**Topic**	**Specific variables**					
Oral informed consent (phone)		**✔**				
Screening questionnaire (phone)	Sex, age, self-reported weight, height, eligibility criteria	**✔**				
Protein intake	Pro55+ screening^37^ (phone)	**✔**				
Protein intake	Combination of three food diaries and three 24-hour dietary recalls		**✔**		**✔**	**✔**
Written informed consent			**✔**			
Cognitive function	MMSE^35^		**✔**			
Physical functioning	400 m walk test^44 45^		**✔**			**✔**
Antropometrics	Measured body height		**✔**			
Antropometrics	Measured body weight		**✔**		**✔**	**✔**
Demographic	Education, household			**✔**		
General characteristics	Perceived health, smoking status			**✔**		**✔**
Body composition	Bioelectrical impedance			**✔**		**✔**
Body composition	Air displacement plethysmography (Dutch site only)			**✔**		**✔**
Physical functioning	SPPB^49^			**✔**		**✔**
Muscle strength	Hand grip strength			**✔**		**✔**
Muscle strength	Leg extension strength			**✔**		**✔**
Self-reported mobility limitations	Ability to walk 400 m and climb one flight of stairs			**✔**	**✔**	**✔**
Risk of sarcopenia	SARC-F Questionnaire^66^			**✔**	**✔**	**✔**
Malnutrition	BMI <22.0 kg/m^2^ or unintentional weight loss >5% in the last 6 months			**✔**		**✔**
Frailty	Frailty Fried Frailty Index^64^			**✔**		**✔**
Quality of Life	EuroQol 5D^63^			**✔**	**✔**	**✔**
Healthcare costs	RUD^67^			**✔**	**✔**	**✔**
Appetite	SNAQ-Appetite^68^			**✔**		**✔**
Physical activity	Accelerometers			**✔**	**✔**	**✔**
Process evaluation						**✔**
*Persuasive technology study*						
Communication style preferences	Personality traits form			**✔**		
Usage data of technology	Practical experiences, interaction data of technology (number of notifications, openings, registered food intake, games)				**✔**	**✔**
Attitude towards technology	Questionnaire					**✔**
*Microbiota study*						
Oral health	Questionnaire			**✔**		**✔**
Oral microbiota	Tongue swab (16S rRNA sequencing)			**✔**		**✔**
Gut microbiota	Fresh frozen faecal sample (16S rRNA sequencing)			**✔**		**✔**
*fMRI study*						
Oral microbiota	Fasted unstimulated salivary sample (16S rRNA sequencing)			**✔**		**✔**
Nutritional and microbial markers	Blood sample			**✔**		**✔**
Appetite	VAS scores of appetite and central neural responses to food-cues measured by fMRI scan			**✔**		**✔**

BMI, body mass index; fMRI, functional MRI; FU, follow-up; MMSE, Mini-Mental State Examination; rRNA, ribosomal RNA; RUD, Resource Utilisation in Dementia; SNAQ, Simplified Nutritional Appetite Questionnaire; SPPB, Short Physical Performance Battery; VAS, Visual Analogue Scale.

### Intervention

Participants in the intervention group 1 will receive a personalised dietary advice face-to-face by nutritionists dedicated to this study aiming at increasing their protein intake to at least 1.2 g/kg aBW/day (without increasing total daily energy intake), based on their habitual dietary characteristics (based on three 24-hour recalls), protein intake and measured BW assessed at baseline. Participants will be asked if they usually prepare the main meal; whether they eat the meal at a for example, community home; whether they consume ready-to-eat meals; whether they use meal services; and if they eat at family or friends’ home. All their answers will be incorporated in the personalised dietary advice. Participants will receive written dietary advice accompanied by a verbal explanation from the nutritionist. Participants can contact the nutritionist at any time by mail or phone in case any question arises. The advice includes the use of regular protein-rich food products and protein-enriched food products provided by the research team, and will be based on personal dietary preferences. Protein-enriched food products that can be incorporated within the regular diet include protein bars, cereals, puddings, coconut water and whey powder, which will be freely provided and shipped to participants’ home. Those products can be incorporated in the dietary advice as they can make it easier to increase protein intake due to their high-protein content.

Participants receive guidelines on how to incorporate the protein-enriched food products within their diet. The dietary advice will also incorporate the advice to consume at least one daily meal consisting of ≥35 g protein, as studies have shown that this amount increases MPS in older adults.^40–42^

Participants in intervention group 2 will receive the same dietary advice as intervention group 1, and the personalised advice to consume at least 7.5–10 g protein through protein-(en)rich(ed) food products within half an hour after performing usual physical activity as this may enhance resistance exercise-induced MPS.^27^ One RCT among older adults has shown that protein supplementation in combination with resistance exercise had beneficial effects on, for example, muscle mass and function, but no differences in effect were found between protein consumption pre-resistance versus post-resistance exercise.^43^ We therefore recommend protein intake after physical activity as this is a uniform and more feasible advice compared with ‘in close proximity of’, and might also result in less stomach discomfort as compared with protein consumption prior to physical activity. Usual physical activity is defined as either physical exercise (eg, biking, swimming, tennis) or the most intensive activities of daily living when the participant does not engage in physical exercise (eg, gardening, housekeeping, doing groceries) for a minimum of 30 min. The advice is linked to most extensive or longest physical activity. Participants are instructed not to become more or less physically active but merely to shift their physical activity or protein intake moment.

During the intervention period, nutritionists will plan follow-up phone calls in consultation with the participants during week 2, week 4, week 8, week 16 and week 20 to ask if they have understood the advice and are able to adhere to the advice. In addition, any issues related to the use of protein-enriched food product can be discussed (intervention groups only). If necessary, changes in the dietary advice will be made, for example when weight change >2 kg has occurred (based on self-assessment). Participants allocated to the control group do not receive any intervention, but are contacted on similar time points as the intervention groups to ask how they are doing.

All participants are invited to a minimum of one organised lecture on non-health-related themes and other social events during the trial in order to stimulate their commitment to the trial. Separate lectures/events (with the same topic) are organised for the intervention groups and the control group to prevent interference between intervention arms. Participants can freely attend those lectures and all travel costs will be reimbursed.

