### Participants’ safety

In case any (medical) questions arise during the screening or intervention period, participants can consult an independent medical doctor. All adverse events and serious adverse advents will be tracked by the nutritionists during the follow-up phone calls, 3-month follow-up visit and 6-month follow-up visit to assess their potential relationship to the intervention at both sites and will be documented in the final report. Adverse events will be reported within 7 days (death or life-threatening situations) or within 15 days (in case of other adverse events) of first knowledge to The Medical Ethical Committee of the Amsterdam UMC, location VUmc (required for the Dutch site only).

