### Patient and public involvement

The PROMISS RCT is designed by the Faculty of Science (VU Amsterdam, the Netherlands) and the Department of General Practice and Primary Health Care (University of Helsinki, Finland) (please see online supplemental appendix 1 for the PROMISS trial group), a collaboration of the EU Horizon 2020 PROMISS Project. Two medical and one ethical advisor are involved in the study. As part of the PROMISS project, we previously performed three pilot studies as a preparation of the long-term PROMISS randomised trial, of which one is published.^71^ We included the feedback of the participants in designing the long-term PROMISS randomised trial; participants enjoyed participating in the pilot studies and they liked the frequent contact with the nutritionist. We also tested which protein-enriched food products they preferred and included those products in the long-term PROMISS randomised trial which they liked the most. Older adults are not involved in recruitment of participants or conduct of the study. Results of this study will be disseminated to participants through sending them a lay abstract with the results and conclusions of the study. At the end of the study, each participant will receive a fact-sheet with personal results of dietary intake data, hand grip strength, body composition measures and BW. Participant burden of the pilot intervention was assessed using informal feedback from older adults participating in one of three pilot studies.

10.1136/bmjopen-2020-040637.supp1Supplementary data

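### Adverse events are tracked by unblinded advice-givers in calls whose stated content differs by arm, so counts by arm are at risk of uneven ascertainment

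*Protocol article*

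**What the plan says.** Participants’ safety states who collects events and when. Events of either kind, serious or not, "will be tracked by the nutritionists during the follow-up phone calls, 3-month follow-up visit and 6-month follow-up visit". The purpose given is to decide whether an event could be linked to the intervention, and the final report is to list the events. An independent doctor is available for participants' questions; no part in judging relatedness is described.

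The Intervention section describes the calls (weeks 2, 4, 8, 16 and 20). In the intervention groups the nutritionists call "to ask if they have understood the advice and are able to adhere to the advice". One further topic is described for these two groups and not for controls: "any issues related to the use of protein-enriched food product can be discussed (intervention groups only". The advice may be changed if needed, with a self-assessed weight change above 2 kg as the example. Controls "are contacted on similar time points as the intervention groups to ask how they are doing".

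The same section has the nutritionists deliver the advice. Randomisation, allocation and masking says that they are not blinded. The limitations list admits that unblinded nutritionists collect the outcome measures, but does not mention adverse events. Patient and public involvement adds that "Two medical and one ethical advisor are involved in the study", without giving their duties.

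**The concern.** How many events are recorded depends on how people are asked. A conversation about problems with protein bars or whey powder is a likely place for minor food-related complaints to surface, and only two of the three arms are described as having it. An open enquiry about well-being may bring out other things, such as general illness. If each arm is asked differently, a difference in counts mixes any true effect with the difference in asking.

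Attribution adds a second risk. A person who composed and coached the advice, and knows who received it, may be slow to link a complaint to it. For a control participant the question of relatedness to the intervention has little content. A table restricted to related events would therefore depend heavily on who judged them.

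The Discussion says the trial should inform whether the recommended protein intake for older adults ought to rise to 1.2 g/kg adjusted body weight per day. Readers with that question in mind will set adverse event counts side by side, whether or not a test is planned.

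**Working it through.** The article gives no adverse event rate and no detection rate, so there is no figure of its own to reproduce here. The sample size calculation concerns walk time and does not bear on this point. The check is mainly a comparison of sections.

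**Step 1. Contacts.** Scheduled contacts at which events are tracked: 5 calls + 2 visits = 7. Calls make up 5/7, about 71%.

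**Step 2. Stated content by arm.**

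| Contact | Intervention groups | Control group |
|---|---|---|
| 5 calls | Understanding, adherence, product problems, possible change of advice | How the person is doing |
| 3-month visit | Common measurements, plus further advice if needed (Compliance) | Common measurements |
| 6-month visit | Common measurements, plus process evaluation questions (Study timeline) | Common measurements |
| Unscheduled | May contact the nutritionist at any time about the advice (Intervention) | None described |

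The timing of calls and visits is similar. The stated content of the calls is not.

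**Step 3. Who asks and who judges.** Participants’ safety names the nutritionists as those who track. The relatedness clause follows in the same sentence with no other assessor named. The Statistical analyses plan blinds the statistician, but that acts after the events have been recorded and cannot repair uneven recording.

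**Step 4. What uneven recording could do (illustration only).** Assume the same true risk R in both arms, detection d₁ in one arm and d₀ in the other, and n = 88 per arm (planned size, no drop-out). Recorded risks are p₁ = R·d₁ and p₀ = R·d₀, so the apparent risk ratio is d₁/d₀ whatever R is. With p̄ = (p₁ + p₀)/2, the chance of a nominally significant difference at two-sided 0.05 is approximately

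Φ{ [ |p₁ − p₀| − 1.96·√(2p̄(1 − p̄)/n) ] / √[ (p₁(1 − p₁) + p₀(1 − p₀))/n ] }.

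Worked case, R = 0.20 with detection 90% against 70%: p₁ = 0.18, p₀ = 0.14, p̄ = 0.16. The numerator is 0.04 − 1.96 × 0.0553 = −0.068 and the denominator is 0.0552, giving Φ(−1.24) = 0.108.

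| Assumed detection | Apparent risk ratio | Chance of a false signal, R from 0.20 to 0.40 |
|---|---|---|
| Equal | 1.00 | 5% |
| 90% v 70% | 0.90/0.70 = 1.29 | 11% to 21% |
| 90% v 50% | 0.90/0.50 = 1.80 | 33% to 66% |

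If the control arm were the better ascertained one, the ratios become 0.70/0.90 = 0.78 and 0.50/0.90 = 0.56. The chances are unchanged, because the formula is symmetric for equal arms. The table shows what the assumptions imply. It is not evidence that such a gap exists.

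**Step 5. The reporting sentence.** Participants’ safety first separates adverse events from serious ones. It then sets 7 days for death or life-threatening situations and "within 15 days (in case of other adverse events) of first knowledge" for the rest. Read literally, the second limb ignores the distinction just drawn. This does not affect the comparison of arms.

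**The case against.** The Intervention section gives the general purpose of the calls, not an adverse event script. Participants’ safety covers all events with no restriction by arm, and a common question may well stand in the full protocol or procedures, which are not shown. Call times are similar, both visits apply to everyone, and no between-arm test of harm is planned. The wording on controls does not say that nothing else is asked. No relatedness assessor is explicitly named, and the medical advisors' duties are simply not described. Direction is open: asking people how they are is a general health question, whereas the stated intervention content contains none, so controls could be the better ascertained arm for general illness.

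Most of this stands, and it limits the claim to a risk of unknown size and direction. It does not remove the claim. The article chose to describe the calls, described them differently by arm, and named the same calls as occasions for collecting adverse events. That is stated content, not a missing detail. Admitting unblinded collection of outcome measures as a limitation does not reach adverse events.

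A reader might also infer that Finnish participants have no expedited reporting, because the reporting rule is marked as required for the Dutch site only. The document does not support that. The rule concerns reporting to the Amsterdam committee. Finland has its own ethics committee, whose requirements are not shown, and tracking is stated for both sites.

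**Conclusion.** The point holds as a risk. As described, unblinded nutritionists who deliver the advice collect adverse events in calls with arm-dependent stated content, so counts by arm may reflect how each arm was asked. That the same nutritionists judge relatedness is the natural reading, not an explicit statement.

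The size and sign of any bias cannot be set from the document. The risk ratios of 1.29 to 1.80, or their mirror images, rest wholly on assumed detection rates, and with equal detection there is no bias. A reader might go further and conclude that harm cannot be compared fairly between arms. That does not follow, because call timing is similar, two visits are common to all arms, and a uniform question may already be in use.

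The 15-day wording is a separate inconsistency with no bearing on the comparison of arms.

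**What to change.** In the Intervention and Participants’ safety sections:

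- State that one identical scripted adverse event question is asked in all three arms at every call and at both visits, before any talk about diet or products. If such a script already exists, say so.
- Report adverse event counts by arm regardless of judged relatedness.
- Name who judges relatedness. For serious events, use one of the existing medical advisors, who does not deliver the advice.
- Reconcile the split between adverse and serious adverse events with the wording of the 15-day limb. This review takes no position on which reporting rule should apply, or on the rules for the Finnish site.

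The cost is a small change to the call script and a little advisor time. No new visits, staff or measurements are needed.

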#### Compliance

We will collect dietary intake prior to the 3-month follow-up visit (by means of the combination of three food diaries and three 24-hour dietary recalls) to assess compliance to the dietary advice. This information allows the nutritionists to provide additional advice—if needed—for participants in the intervention groups, which will be provided during the 3-month follow-up visit. Dietary intake will again be assessed at follow-up and compliance to the dietary advice will be determined.

#### Intervention fidelity

To ensure good adherence to the intervention protocols at both study sites, all personnel working for the trial have undergone extensive training. The nutritionists will follow written standardised operational procedures to develop and provide the personalised dietary advice (with or without additional advice to consume protein within half an hour after usual physical activity). Four times during the conduct of the trial, the nutritionists from one site will visit the other site to attend assessments, and potentially notice and correct differences in order to ensure identical execution of the trial at both sites. In addition, monthly Skype meetings will be held between all staff involved in the execution of the trial at both sites to solve any potential day-to-day issues in a standardised way. Furthermore, identical participant brochures and other printed materials have been developed and translated to Dutch and Finnish language.

### Outcomes

#### Primary outcome

The primary outcome of the PROMISS trial is a 6-month change in physical functioning measured by change in walk time using a 400 m walk test (Long Distance Corridor Walk).^44 45^ This test is predictive for higher risk of mortality, incident cardiovascular disease, and mobility limitation and disability.^46^ One advantage of this continuous outcome is that it enables discrimination between categories of risk among participants,^47^ and it is less prone to a ceiling effect as compared with other functional outcome measures (eg, SPPB).^48^ The course for the 400 m test is 20 m long and marked by a traffic cone and tape line at the beginning and end. For all participants, the test will begin with a mandatory 40 m walk (warm-up) at their usual pace. Thereafter, the 400 m test starts with the feet behind and just touching the starting line and ends after 10 complete rounds when one foot is behind the end line. For the 400 m test, older adults will be instructed to walk as fast as possible at a pace they can maintain for 400 m. Standardised encouragement will be given each lap, including the number of laps remaining. At the 6-month follow-up visit, older adults are allowed to use a cane, can take a rest as needed (but no rest longer than 60 s) and there will be a time limit of 17 min. Time will be recorded to the nearest second.

#### Secondary outcomes

The secondary outcomes are changes in physical performance, muscle strength, body composition, self-reported mobility limitations, QoL, incidence of frailty, incidence of sarcopenia risk and incidence of malnutrition. We will also investigate change in healthcare costs.

Physical performance will be assessed by means of the SPPB.^49^ The SPPB assesses lower extremity function which consists of three timed tests: repeated (five times) chair stand test, 4-metre walk test and three standing balance tests (ability to stand with the feet together in the side-by-side, semitandem and tandem positions). The total score ranges from 0 to 12. A higher score indicates better physical functioning.

Muscle strength will be determined by hand grip strength (kg). Hand grip strength is an indicator of overall muscle strength^50^ and a higher hand grip strength is associated with decreased risk of physical disabilities^51^ and all-cause mortality in old age.^51 52^ Maximum grip strength will be measured three times at each hand during baseline and 6-month follow-up visit. We will use a digital dynamometer (Saehan Digital Handheld Dynamometer) adjusted for hand size. Participants will be measured in an upright sitting position with the forearms supported by the armrest of a chair according to a standardised protocol.^53^ The mean of the maximum score of left and right hand will be used for analyses. Muscle strength will also be determined by leg extension strength (N). A higher leg extension strength is associated with decreased risk of mobility disability^54 55^ and lower risk of early mortality.^56–58^ Leg extension strength will be assessed using a chair designed to measure leg extension strength.^59^ Maximum leg extension strength will be measured three times for each leg during baseline and 6-month follow-up visit. The mean of the maximum score of left and right leg will be used for analyses.

Body composition will be estimated by means of bioelectrical impedance using the BodyStat 1500MDD device, using the Kyle equation to determine fat percentage (%), fat mass and fat-free mass^60^ and the Sergi equation to determine appendicular skeletal muscle mass (kg).^61^ Additionally, at the Dutch study site, body composition (fat free mass (kg), fat mass and fat percentage (%)) will be measured by air displacement plethysmography.^62^

Self-reported mobility limitations will be assessed by means of a questionnaire; ‘Because of your health, how much difficulty do you have walking 400 metre?’ and ‘Because of your health, how much difficulty do you have climbing 10 steps?’ Participants will respond using a 5-level Likert scale: ‘no difficulty’, ‘a little difficulty’, ‘some difficulty’, ‘a lot of difficulty’ and ‘unable to do the activity’. Mobility limitation is defined as two consecutive reports of having any difficulty walking 400 m or climbing 10 steps without resting due to a health or a physical problem.

QoL will be measured using the EuroQol 5D-5 L Questionnaire.^63^

Incident frailty will be assessed using the Fried criteria.^64^ Participants will be considered ‘frail’ when three or more components are present. Those with no components will be considered ’robust’, whereas those with one or two components will be considered ’prefrail’. The criteria include (1) self-reported unintentional weight loss (>4 kg in past 6 months), (2) self-reported exhaustion (based on two questions from the Center for Epidemiologic Studies Depression Scale on exhaustion in the past week at baseline and follow-up: ‘I felt that everything I did was an effort’ and ‘I could not get going’. Scores range from 1 ‘rarely or none of the time’ to 4 ‘always or most of the time’. A score of 3 or 4 on either question indicates exhaustion,^65^ (3) weakness (grip strength in the lowest 20% of the whole study population based on the mean of the maximum scores, adjusted for gender and BMI), (4) slow walking speed (walk time on the 4 m walk test in the slowest 20% of the whole study population, adjusted for gender and height), and (5) low physical activity (total counts per week based on the accelerometer data in the lowest 20% of physical activity for each gender). Incident frailty is considered deterioration of frailty status; that is, from robust at baseline to prefrail or frail at follow-up or from prefrail at baseline to frail at follow. Frail participants at baseline will be excluded from these analyses.

Incidence of sarcopenia risk will be assessed with the SARC-F Questionnaire^66^; how much effort do you experience when (1) lifting and carrying a bag of 4.5 kilo, (2) walking across a room, (3) transferring from a chair or bed, (4) climbing a flight of 10 stairs and (5) how many times have you fallen in the past year. Answering option include no effort (0 points), a bit of effort (1 point) and a lot of effort (2 points), where a score equal to or greater than 4 is predictive of sarcopenia and poor outcomes. Participants with risk of sarcopenia at baseline will be excluded from these analyses.

Incidence of malnutrition will be defined as BMI <22.0 kg/m^2^ or unintentional weight loss >5% in the last 6 months. Malnourished participants at baseline will be excluded from these analyses.

A modified version of the Resource Utilisation in Dementia Questionnaire^67^ will be used to collect data on healthcare and social utilisation costs over the period 3 months prior to baseline, 3 months prior to the 3-month follow-up visit and 3 months prior to 6-month follow-up visit. Costs include costs of primary and secondary care, complementary care, informal care and home care.

